### **20.2 Clinical Laboratory Evaluations**

[figure not shown]

Descriptive statistics for mean and mean changes in clinical laboratory tests (hematology, chemistry, and coagulation) will be presented by study visit for each treatment group.

Potentially clinically significant (PCS) clinical laboratory results will be determined based on normal limits and the worst post-baseline value using the definitions shown below for each test. Summaries of the number and percentage (%) of subjects meeting PCS criteria will be generated using the subgroup of subjects in the safety analyses set that have both a baseline and any post-baseline laboratory evaluation.

Shift tables will be presented to show the number and percentage of subjects with a laboratory value below the lower limit of normal (LLN), within normal limits, above the upper limit of normal (ULN) and missing at baseline versus the value at each visit and the worst post-baseline value. Percentages for each laboratory test will be based on the number of subjects in the Safety analyses set.

**Table 3: Potential Clinical Significance (PCS) for Hematology Parameters**

| Laboratory Parameter                           | Flag | Criteria*          |                                 |
|-------------------------------------------------------|-------------|---------------------------|---------------------------------|
|                                                       |             | Observed Value     | Change from Baseline     |
| Hemoglobin (g/L)                                      | High (CH)   | $>1.3 \times \text{ULN}$  | $>30\%$ Increase from Baseline  |
|                                                       | Low (CL)    | $<0.8 \times \text{LLN}$  | $>20\%$ Decrease from Baseline  |
| Hematocrit (%)                                        | High (CH)   | $>1.3 \times \text{ULN}$  | $>30\%$ Increase from Baseline  |
|                                                       | Low (CL)    | $<0.8 \times \text{LLN}$  | $>20\%$ Decrease from Baseline  |
| Erythrocyte count (RBC) ( $10^{12}/\text{L}$ )        | High (CH)   | $>1.3 \times \text{ULN}$  | $>30\%$ Increase from Baseline  |
|                                                       | Low (CL)    | $<0.8 \times \text{LLN}$  | $>20\%$ Decrease from Baseline  |
| Mean corpuscular Volume (MCV) (fL)                    | High (CH)   | $>1.15 \times \text{ULN}$ | $>15\%$ Increase from Baseline  |
|                                                       | Low (CL)    | $<0.85 \times \text{LLN}$ | $>15\%$ Decrease from Baseline  |
| Mean corpuscular hemoglobin (MCH) (pg)                | High (CH)   | $>1.15 \times \text{ULN}$ | $>15\%$ Increase from Baseline  |
|                                                       | Low (CL)    | $<0.85 \times \text{LLN}$ | $>15\%$ Decrease from Baseline  |
| Mean corpuscular hemoglobin concentration (MCHC)(g/L) | High (CH)   | $>1.15 \times \text{ULN}$ | $>15\%$ Increase from Baseline  |
|                                                       | Low (CL)    | $<0.85 \times \text{LLN}$ | $>15\%$ Decrease from Baseline  |
| Leukocyte count (WBC)( $10^9/\text{L}$ )              | High (CH)   | $>1.6 \times \text{ULN}$  | $>100\%$ Increase from Baseline |
|                                                       | Low (CL)    | $<0.65 \times \text{LLN}$ | $>60\%$ Decrease from Baseline  |
| Neutrophils (%)                                       | High (CH)   | $>1.6 \times \text{ULN}$  | $>100\%$ Increase from Baseline |
|                                                       | Low (CL)    | $<0.65 \times \text{LLN}$ | $>75\%$ Decrease from Baseline  |
| Lymphocytes(%)                                        | High (CH)   | $>1.5 \times \text{ULN}$  | $>100\%$ Increase from Baseline |
|                                                       | Low (CL)    | $<0.25 \times \text{LLN}$ | $>75\%$ Decrease from Baseline  |
| Eosinophils(%)                                        | High (CH)   | $>4.0 \times \text{ULN}$  | $>300\%$ Increase from Baseline |
|                                                       | Low (CL)    | N/A                       | N/A                             |
| Monocytes(%)                                          | High (CH)   | $>4.0 \times \text{ULN}$  | $>300\%$ Increase from Baseline |
|                                                       | Low (CL)    | N/A                       | N/A                             |
| Basophils(%)                                          | High (CH)   | $>4.0 \times \text{ULN}$  | $>300\%$ Increase from Baseline |
|                                                       | Low (CL)    | N/A                       | N/A                             |
| Platelets ( $10^9/\text{L}$ )                         | High (CH)   | $>1.5 \times \text{ULN}$  | $>100\%$ Increase from Baseline |
|                                                       | Low (CL)    | $<0.65 \times \text{LLN}$ | $>50\%$ Decrease from Baseline  |

[figure not shown]

Notes: PCS = potentially clinically significant, ULN= upper limit of normal, LLN= lower limit of normal  
CH = high PCS based on criterion value and increase from baseline.  
CL = low PCS based on criterion value and decrease from baseline.  
N/A= Not Applicable

\*A post-dose value is considered as a PCS value if it meets both criteria for observed value and change from baseline

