## Statistical Analysis Plan (SAP) for Protocol W-4873-301

kSubjects with a PORT score of 51 to 105 (PORT Risk Class of II, III or IV) are eligible for enrolment.

lAt Screening, local laboratory evaluations required for assessing subject eligibility include serum aminotransferase (ALT and AST) and total bilirubin levels, serum creatinine and blood urea nitrogen (or urea), peripheral white blood cell (WBC) count, absolute neutrophil count, coagulation and immature neutrophil percentage and serology for HIV. Blood will be collected for central laboratory testing at the Screening, Day 3, EOT and TOC visits. Local laboratory evaluations will be conducted at FU in subjects with clinically significant laboratory abnormalities noted at or after the TOC Visit.

mCollect blood for acute (Screening) and convalescent (TOC) atypical pathogen serology, including *M. pneumoniae*, *C. pneumoniae* and *L. pneumophila*, for central laboratory testing.

nAt Screening, a urine dipstick will be performed locally; if results are abnormal and deemed clinically significant by the Investigator, a urinalysis will be sent to the central laboratory.

oAt Screening, urine will be collected for central laboratory testing of *S. pneumoniae* and *L. pneumophila*. These tests will be done by the central laboratory using rapid antigen test kits

pAt Screening, a local laboratory urine or serum pregnancy test (females only) is required to confirm study eligibility. In addition, blood will be collected from all female subjects for serum  $\beta$ -human chorionic gonadotropin pregnancy test by the central laboratory at the Screening and TOC visits.

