## **18.3 Safety Endpoints**

- Incidence of treatment-emergent adverse events (TEAEs), serious adverse events (SAEs) and discontinuations due to TEAEs
- Incidence of potentially clinically significant (PCS) changes in safety laboratory parameters, vital signs and electrocardiograms (ECGs)

[figure not shown]

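### The high-neutrophil PCS rule cannot be met if the laboratory ULN is 62.5% or more, and the low rule, also on percentages, can miss large falls in the absolute count

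*SAP*

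**What the plan says.** SAP section 18.3 lists as a safety endpoint "Incidence of potentially clinically significant (PCS) changes in safety laboratory parameters, vital signs and electrocardiograms (ECGs"). For haematology, section 20.2 applies the Table 3 criteria to the worst post-baseline value.

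Table 3 gives neutrophils only as a percentage:

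- High: "Neutrophils (%) | High (CH) | $>1.6 \times \text{ULN}$ | $>100\%$ Increase from Baseline".
- Low: "Low (CL) | $<0.65 \times \text{LLN}$ | $>75\%$ Decrease from Baseline".

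The table footnote joins the two columns: "A post-dose value is considered as a PCS value if it meets both criteria for observed value and change from baseline". The WBC row, which is a count in 10^9/L, has the same high limits as the neutrophil row (1.6 × ULN and a rise above 100%). Its low rule is "Low (CL) | $<0.65 \times \text{LLN}$ | $>60\%$ Decrease from Baseline".

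Table 3 has no row for the absolute neutrophil count. Footnote l of the schedule in section 8 names that count among the local eligibility tests at Screening ("absolute neutrophil count, coagulation and immature neutrophil percentage"). The SAP states no ULN or lower limit of normal (LLN) for any haematology parameter.

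**The concern.** Multiples of a reference limit suit a quantity with no ceiling, such as a cell count. The neutrophil row applies the WBC multiplier to a percentage, which stops at 100. If the cut-off is at or above 100%, the row shows no cases in either arm whatever the drug does, and a reader of the table could take that for evidence of no effect.

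The low row has a different weakness. A neutrophil percentage does not carry the fall in total white cells. When both fall, each row sees only part of the change, and neither may reach its own limit although the absolute neutrophil count has dropped steeply.

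**Working it through.** The plan states no figure to reproduce here. The inputs are the Table 3 multipliers and change criteria, plus assumed reference limits because the SAP gives none.

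**High rule, observed value.** The cut-off is 1.6 × ULN, and it must lie below 100% to be reachable. Break-even ULN = 100/1.6 = 62.5%.

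| Assumed ULN (%) | 1.6 × ULN (%) | Reachable |
|---|---|---|
| 60 | 96 | yes |
| 62.5 | 100 | no (the rule needs a value above 100) |
| 65 | 104 | no |
| 70 | 112 | no |
| 75 | 120 | no |
| 80 | 128 | no |

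**High rule, change.** A rise above 100% means a value more than twice baseline. Since the value is at most 100%, baseline must be below 50%. At ULN 60% a flag therefore needs a move from under 50% to over 96%.

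**Low rule.** The observed part needs a value below 0.65 × LLN. For an assumed LLN of 35% to 50% that is below 22.75% to 32.5%. The change part needs a value below 0.25 × baseline: 15, 17.5, 20 and 22.5% for baselines of 60, 70, 80 and 90%. Across these ranges the change part is the stricter one. The rule can be met.

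**Joint falls.** Absolute count = WBC × neutrophil %/100. Assumed limits: WBC LLN 4.0 (0.65 × 4.0 = 2.6) and neutrophil LLN 40% (0.65 × 40 = 26%).

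1. WBC 5.0 to 2.2, neutrophils 80% to 21%.
   - Absolute count: 5.0 × 0.80 = 4.0 to 2.2 × 0.21 = 0.46, a fall of 88%.
   - WBC falls 2.8/5.0 = 56%, short of 60%. The percentage falls 59/80 = 74%, short of 75%.
   - Neither row flags it. Both change criteria fail, so this holds for any LLN.
2. WBC 15 to 3.0, neutrophils 85% to 25%.
   - Absolute count: 12.75 to 0.75, a fall of 94%.
   - The percentage falls 60/85 = 70.6%, short of 75%. WBC 3.0 is above 2.6.
   - Neither row flags it. The WBC part depends on the assumed LLN of 4.0.
3. WBC 12 to 1.5, neutrophils 80% to 30%.
   - Absolute count: 9.6 to 0.45, a fall of 95%.
   - The neutrophil row does not flag it (30% is above 26%, and the fall is 62.5%).
   - The WBC row does (1.5 is below 2.6, and the fall is 87.5%).

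**The same low multipliers on the absolute count.** For an assumed absolute LLN of 1.8 to 2.0, 0.65 × LLN is 1.17 to 1.30. The end values 0.46, 0.75 and 0.45 are all below this and all three falls exceed 75%, so every case would be flagged.

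**The case against.** The strongest reply is that the harm is small and the values are not hidden. Section 20.2 also plans means, mean changes and shift tables, classing values as below, within or "above the upper limit of normal (ULN) and missing at baseline versus the value at each visit and the worst post-baseline value". All laboratory data are listed with out-of-range values flagged, and adverse events are tabulated separately. In case 1, WBC 2.2 and neutrophils 21% both lie below the assumed lower limits and would show in the shift tables. The WBC row gives marked leukocytosis a working PCS rule and catches some joint falls, as in case 3. PCS results are descriptive, with no test attached. All of this stands and limits the point to the neutrophil PCS counts. It does not repair them: a shift table does not grade the size of an abnormality, and a row that cannot be met gives no information.

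Three stronger readings are tempting, and the document does not support them:

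- A reader might infer that the high row is certain to show zero in both arms. That depends on a ULN the SAP does not give; below 62.5% the row is reachable, though nearly empty.
- A reader might infer that the low rule is equally impossible, or that such falls vanish from the whole PCS table. The low rule is reachable. In case 1 the other cell types make up 79% of the differential, so the lymphocyte row could flag a high value, though not as a neutrophil finding.
- A reader might infer that subjects with an eosinophil or basophil percentage of zero at baseline can never be flagged. The SAP only leaves the percentage change from zero unspecified. Moving to absolute counts would not settle it.

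**Conclusion.** The point holds in a limited form. For any ULN of 62.5% or more, the high-neutrophil PCS rule cannot flag anyone in either arm; below that it is close to empty. This follows from the multiplier and the 100% ceiling; only the ULN is assumed. The low rule works but can miss absolute falls of about 90% when WBC falls too, and the WBC row does not catch every such case. How often this would happen cannot be estimated from the SAP.

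The consequence is confined to the neutrophil PCS counts within a listed safety endpoint. Other safety displays still show out-of-range values, and the efficacy analyses are unaffected. The row is worth correcting because it is wrong as written and inexpensive to change.

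**What to change.** In Table 3, replace the neutrophil percentage row with one for the absolute neutrophil count (10^9/L), taken as reported or derived as WBC × neutrophil %/100. Derive it sample by sample before selecting the worst post-baseline value, so that results from different visits are not multiplied together. The sponsor should confirm the multipliers, change criteria and reference range for that scale; the present ones need not carry over unchanged. Keep the percentage in the descriptive and shift tables only. Limits that fit within 0 to 100% would make the high row reachable but would leave the joint-fall gap.

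The cost is a SAP wording and programming change, one derived variable and an absolute-count reference range. WBC and the neutrophil percentage are already Table 3 parameters, so no new measurement is needed. A short note on how percentage change is handled when baseline is zero could be added at the same time.

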**Table 4: Potential Clinical Significance (PCS) for Serum Chemistry Parameters**

| Laboratory Parameter                 | Flag      | Criteria*                 |                                 |
|--------------------------------------|-----------|---------------------------|---------------------------------|
|                                      |           | Observed Value            | Change from Baseline            |
| Bicarbonate (mmol/L)                 | High (CH) | $>1.3 \times \text{ULN}$  | $>40\%$ Increase from Baseline  |
|                                      | Low (CL)  | $<0.7 \times \text{LLN}$  | $>40\%$ Decrease from Baseline  |
| Sodium (mmol/L)                      | High (CH) | $>1.1 \times \text{ULN}$  | $>10\%$ Increase from Baseline  |
|                                      | Low (CL)  | $<0.85 \times \text{LLN}$ | $>10\%$ Decrease from Baseline  |
| Potassium (mmol/L)                   | High (CH) | $>1.2 \times \text{ULN}$  | $>20\%$ Increase from Baseline  |
|                                      | Low (CL)  | $<0.8 \times \text{LLN}$  | $>20\%$ Decrease from Baseline  |
| Magnesium(mmol/L)                    | High (CH) | $>3.0 \times \text{ULN}$  | $>200\%$ Increase from Baseline |
|                                      | Low (CL)  | $<0.5 \times \text{LLN}$  | $>65\%$ Decrease from Baseline  |
| Phosphorus (mmol/L)                  | High (CH) | $>3.0 \times \text{ULN}$  | $>200\%$ Increase from Baseline |
|                                      | Low (CL)  | $<0.5 \times \text{LLN}$  | $>50\%$ Decrease from Baseline  |
| Chloride (mmol/L)                    | High (CH) | $>1.2 \times \text{ULN}$  | $>20\%$ Increase from Baseline  |
|                                      | Low (CL)  | $<0.8 \times \text{LLN}$  | $>20\%$ Decrease from Baseline  |
| Calcium (mmol/L)                     | High (CH) | $>1.3 \times \text{ULN}$  | $>30\%$ Increase from Baseline  |
|                                      | Low (CL)  | $<0.7 \times \text{LLN}$  | $>30\%$ Decrease from Baseline  |
| Alkaline phosphatase (ALP)(U/L)      | High (CH) | $>2.0 \times \text{ULN}$  | $>100\%$ Increase from Baseline |
|                                      | Low (CL)  | $<0.5 \times \text{LLN}$  | $>80\%$ Decrease from Baseline  |
| Alanine aminotransferase(ALT)(U/L)   | High (CH) | $>3.0 \times \text{ULN}$  | $>200\%$ Increase from Baseline |
|                                      | Low (CL)  | N/A                       | N/A                             |
| Aspartate aminotransferase(AST)(U/L) | High (CH) | $>3.0 \times \text{ULN}$  | $>200\%$ Increase from Baseline |
|                                      | Low (CL)  | N/A                       | N/A                             |
| Gamma-glutamyltransferase(U/L)       | High (CH) | $>3.0 \times \text{ULN}$  | $>200\%$ Increase from Baseline |
|                                      | Low (CL)  | N/A                       | N/A                             |
| Lactate dehydrogenase (LDH)(U/L)     | High (CH) | $>4.0 \times \text{ULN}$  | $>300\%$ Increase from Baseline |
|                                      | Low (CL)  | $<0.4 \times \text{LLN}$  | $>60\%$ Decrease from Baseline  |
| Bilirubin, Total (umol/L)            | High (CH) | $>2.5 \times \text{ULN}$  | $>150\%$ Increase from Baseline |
|                                      | Low (CL)  | N/A                       | N/A                             |
| Bilirubin, Direct (umol/L)           | High (CH) | $>2.5 \times \text{ULN}$  | $>150\%$ Increase from Baseline |
|                                      | Low (CL)  | N/A                       | N/A                             |
| Glucose, non-fasting (mmol/L)        | High (CH) | $>3.0 \times \text{ULN}$  | $>200\%$ Increase from Baseline |
|                                      | Low (CL)  | $<0.6 \times \text{LLN}$  | $>40\%$ Decrease from Baseline  |
| Protein, Total (g/L)                 | High (CH) | $>1.5 \times \text{ULN}$  | $>50\%$ Increase from Baseline  |
|                                      | Low (CL)  | $<0.5 \times \text{LLN}$  | $>50\%$ Decrease from Baseline  |
| Albumin (g/L)                        | High (CH) | $>1.5 \times \text{ULN}$  | $>50\%$ Increase from Baseline  |
|                                      | Low (CL)  | $<0.5 \times \text{LLN}$  | $>50\%$ Decrease from Baseline  |
| Serum creatinine (umol/L)            | High (CH) | $>2.0 \times \text{ULN}$  | $>100\%$ Increase from Baseline |

## Statistical Analysis Plan (SAP) for Protocol W-4873-301

[figure not shown]

|                                       |           |                          |                                 |
|---------------------------------------|-----------|--------------------------|---------------------------------|
|                                       | Low (CL)  | N/A                      | N/A                             |
| Blood Urea Nitrogen (BUN)
(mmol/L) | High (CH) | $>3.0 \times \text{ULN}$ | $>200\%$ Increase from Baseline |
|                                       | Low (CL)  | N/A                      | N/A                             |

Notes: PCS = potentially clinically significant, ULN= upper limit of normal, LLN= lower limit of normal

CH = high PCS based on criterion value and increase from baseline.

CL = low PCS based on criterion value and decrease from baseline.

N/A= Not Applicable

\* A post-dose value is considered as a PCS value if it meets both criteria for observed value and change from baseline.

For the calculated creatinine clearance, shifts from baseline to lowest post-baseline value will be presented using the cut-offs:  $< 30$ ,  $30-60$ ,  $> 60-90$ ,  $> 90$  (mL/min), missing. Within each cross-tabulation, the number and percent of subjects will be tabulated.

For subjects with normal liver parameters (on a per-analyte basis) at baseline, the number and percentage of subjects with the following liver chemistry parameters will be summarized:

- $\text{ALT} \geq 3 \times \text{ULN}$ ,  $\geq 5 \times \text{ULN}$ ,  $\geq 10 \times \text{ULN}$
- $\text{AST} \geq 3 \times \text{ULN}$ ,  $\geq 5 \times \text{ULN}$ ,  $\geq 10 \times \text{ULN}$ ,
- Total bilirubin  $> 1.5 \times \text{ULN}$  and  $> 2 \times \text{ULN}$
- Alkaline Phosphatase (ALP)  $\geq 1.5 \times \text{ULN}$  and  $\geq 2 \times \text{ULN}$
- $\text{ALT} \geq 3 \times \text{ULN}$  and Total bilirubin  $> 1.5 \times \text{ULN}$
- $\text{AST} \geq 3 \times \text{ULN}$  and Total bilirubin  $> 2 \times \text{ULN}$
- Potential Hy's Law cases: ALT or AST  $\geq 3 \times \text{ULN}$ , Total bilirubin  $> 2 \times \text{ULN}$ , and ALP  $\leq 2 \times \text{ULN}$  (where each individual result does not need to occur in the same blood draw)

All clinical laboratory data will be listed. Values outside the normal ranges will be flagged.

The coagulation parameters: partial thromboplastin time (PTT), prothrombin time (PT) and International Normalized ratio (INR) was collected using local laboratories but the normal ranges were not obtained. The number and percentage of subjects with PCS changes in the international normalized ratio only will be presented by treatment group, based on the threshold in Table.

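### Potential Hy's Law cases are counted only in subjects with normal baseline liver values, so a subject with raised baseline values can meet the SAP's own criteria and go uncounted

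*SAP*

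**What the plan says.** Four parts of SAP Section 20.2 bear on this point.

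- **Liver-threshold list (after Table 4).** The lead-in reads "For subjects with normal liver parameters (on a per-analyte basis) at baseline, the number and percentage of subjects with the following liver chemistry parameters". Beneath it are rows for ALT, AST, total bilirubin and ALP alone, two paired rows, and a last row beginning "Potential Hy's Law cases: ALT or AST". That last row requires ALT or AST ≥3×ULN, total bilirubin >2×ULN and ALP ≤2×ULN, and adds "where each individual result does not need to occur in the same blood draw".
- **PCS rule (Table 4 and its footnote).** ALT and AST are each flagged high at >3.0×ULN with a rise of more than 200%. Total bilirubin is flagged high at >2.5×ULN with a rise of more than 150%. The two parts are joined: "A post-dose value is considered as a PCS value if it meets both criteria for observed value and change from baseline".
- **Shift tables.** For each test, subjects are classed as "below the lower limit of normal (LLN), within normal limits, above the upper limit of normal (ULN) and missing at baseline", against each visit and the worst post-baseline value. Percentages are based on the Safety set, with no normal-baseline restriction.
- **Listings.** All laboratory data are listed and out-of-range values flagged. No listing of Hy's Law cases is named.

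The screening laboratory footnote in Section 8 says ALT, AST and total bilirubin are used to assess eligibility, but gives no cut-offs.

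**The concern.** A Hy's Law row is a screen for a rare combination. Letting its components come from different blood draws makes this screen sensitive. The normal-baseline lead-in works against that, because it leaves out subjects who entered with abnormal liver tests. The row could read zero while a subject in the Safety set meets its laboratory criteria.

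The remaining outputs would have to pick such a subject up. The PCS flag demands a larger peak the higher the baseline. The shift tables take one test at a time and do not grade values above ULN. Overall safety is a primary objective (Section 5.1) and PCS laboratory change is a named safety endpoint (Section 18.3), so a count that can miss qualifying subjects deserves attention.

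**Working it through.** The SAP states no figure for this point that could be reproduced. The check applies its thresholds to constructed subjects, with values in multiples of ULN. Baselines above ULN are an assumption, shown from 1.2 to 3.0×ULN for ALT.

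**1. What the PCS flag requires.** A rise of more than 200% means post-baseline > 3 × baseline, and a rise of more than 150% means post-baseline > 2.5 × baseline. With the observed-value criteria:

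- ALT or AST PCS: post > max(3, 3 × baseline)
- Bilirubin PCS: post > max(2.5, 2.5 × baseline)

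| Baseline ALT (×ULN) | ALT PCS needs more than | Meets the Hy's Law ALT component, not ALT PCS |
|---|---|---|
| 1.2 | 3.6 | 3 to 3.6 |
| 1.5 | 4.5 | 3 to 4.5 |
| 2.0 | 6.0 | 3 to 6.0 |
| 3.0 | 9.0 | 3 to 9.0 |

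For bilirubin, a peak above 2 and up to 2.5×ULN meets the Hy's Law component but is never PCS. From a baseline of 1.2×ULN the gap runs to 2.5 × 1.2 = 3.0×ULN.

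**2. Constructed subjects.** All have ALP 0.8 at baseline and 1.2 at peak, and all meet the Hy's Law laboratory criteria.

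| Subject | ALT | AST | Bilirubin |
|---|---|---|---|
| A | 1.5 to 4.0 (+167%) | 0.9 to 2.0 | 0.8 to 2.2 (+175%) |
| C | 1.5 to 4.0 (+167%) | 1.4 to 3.5 (+150%) | 1.2 to 2.8 (+133%) |
| D | 1.5 to 6.0 (+300%) | 0.9 to 4.0 (+344%) | 0.8 to 3.0 (+275%) |

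The percentages are peak/baseline − 1; for example 4.0/1.5 − 1 = 167%, and 2.8/1.2 − 1 = 133%.

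- **A** has no PCS flag and is in neither the ALT rows nor the Hy's Law row. Baseline bilirubin was normal, so A is in the bilirubin >1.5 and >2×ULN rows. In the shift tables, ALT is high-to-high and bilirubin normal-to-high.
- **C** has no PCS flag and is in no liver-threshold row. ALT, AST and bilirubin each appear as high-to-high in the shift tables, as unchanged high values would.
- **D** is PCS-flagged for ALT, AST and bilirubin, and is in the AST and bilirubin rows.

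**3. The composite row.** Two readings of the per-analyte rule are open. If every component must be normal at baseline, none of A, C and D is counted as a potential Hy's Law case. If it is enough that bilirubin and the qualifying aminotransferase were normal, D is counted through AST (0.9 to 4.0), and A and C are still missed. Under the first reading, a baseline ALP of 1.1×ULN would also exclude a subject, although the criterion itself accepts ALP up to 2×ULN. Two programmers could report different counts from the same data.

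**The case against.** The strongest reply is that these subjects are not hidden. The shift tables cover the Safety set without a baseline filter, so every subject with laboratory data is in them. The per-analyte wording keeps a subject with raised ALT but normal bilirubin in the bilirubin rows, and in the AST rows if AST was normal and reached 3×ULN. All values are listed, and the adverse event tables have no baseline restriction. This stands. A reader might infer that such a subject would appear in no table at all; the SAP does not support that. What remains is that none of these outputs is sure to show the combination of aminotransferase and bilirubin that defines the case.

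A second reply is that requiring both an observed value and a change is a deliberate rule, used throughout Tables 3 and 4 to separate new change from existing abnormality. That is reasonable, and the PCS rule is not itself an error. It simply cannot stand in for an unrestricted Hy's Law count.

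Third, the eligibility limits are not in the SAP and may leave few or no subjects with baselines above ULN. This limits the size of the problem and cannot be settled from the SAP.

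A reader might also see a contradiction in the paired rows, where ALT goes with bilirubin >1.5×ULN and AST with bilirubin >2×ULN. These are separate descriptive rows. Different cut-offs are an asymmetry and form no part of this point.

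**Conclusion.** The point holds in limited form. The SAP's only Hy's Law count sits under a normal-baseline restriction whose meaning for composite rows is undefined. A subject with raised baseline ALT, AST or bilirubin can meet the criteria without being counted, and can also miss the ALT or AST PCS flag. In the worst case shown, with all three raised at baseline, the only traces specific to that subject's liver tests are high-to-high shifts and the general listings.

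This assumes that eligibility allows some baselines above ULN. The number of subjects affected cannot be estimated from the SAP and may be small. A reader might infer that a single missed case would change the trial's conclusion. The SAP sets no hepatic decision rule or test, so that does not follow; the consequence is possible under-reporting of a rare safety signal. The change is worth making because it is cheap, and the primary efficacy analysis is untouched.

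**What to change.** In Section 20.2:

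1. Tabulate all the liver thresholds, including potential Hy's Law cases, in every Safety subject with post-baseline data, split by baseline ≤ULN versus >ULN. The normal-baseline count now planned is kept as one part of the split.
2. List every potential Hy's Law case, whatever the baseline values.
3. State how the per-analyte rule assigns a subject to the baseline split in composite rows: which components must be ≤ULN, and whether ALP is one of them.

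The cost is one extra column group in a planned table and one short listing, from data already collected. The drawback is that some counted cases will reflect abnormality present before treatment; the baseline split makes that visible.

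### The different-draw allowance in the potential Hy's Law row also covers the ALP upper bound, so a single ALP ≤2 × ULN meets it; the paired ALT and AST rows use different bilirubin cut-offs

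*SAP*

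**What the plan says.** The liver list follows Table 4 in SAP section 20.2. It is restricted by the words "For subjects with normal liver parameters (on a per-analyte basis) at baseline". Its last row begins "Potential Hy's Law cases: ALT or AST" and requires three things: ALT or AST ≥3 × ULN, total bilirubin >2 × ULN, and ALP ≤2 × ULN. The timing clause attached to it reads "where each individual result does not need to occur in the same blood draw". The clause makes no exception for ALP, sets no time window, and does not say whether the baseline draw counts.

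Just above it are two paired rows. One combines ALT ≥3 × ULN with bilirubin >1.5 × ULN, the other AST ≥3 × ULN with bilirubin >2 × ULN. No reason is given for the difference.

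On the draws available, footnote l of the schedule in section 8 says "Blood will be collected for central laboratory testing at the Screening, Day 3, EOT and TOC visits". It adds local testing at FU for subjects with clinically significant abnormalities at or after TOC. Section 6 also allows unscheduled visits.

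**The concern.** Taking the transaminase peak and the bilirubin peak from different draws is a reasonable way to widen a search for elevations. ALP works the other way. It is a ceiling, there to set aside subjects whose injury looks cholestatic. If any draw may supply the ALP value, a value taken before the injury, or after recovery, satisfies the ceiling, although neither describes the liver when ALT/AST and bilirubin were raised. Subjects in these rows start from normal values, so an early ALP ≤2 × ULN would be unsurprising.

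The mismatch in the paired rows is a separate matter. AST ≥3 × ULN with bilirubin above 1.5 × and up to 2 × ULN, without ALT ≥3 × ULN, falls in no combination row, while the same finding on ALT does.

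Overall safety is a primary objective (section 5.1), and a potential Hy's Law count is small and closely read. The rule should give the same count whoever programs it.

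**Working it through.** The SAP gives no figure to reproduce here. The check is on the logic of the rule.

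**Step 1: a worked subject.** Invented values, as multiples of ULN, at the three scheduled post-baseline central draws:

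| | Day 3 | EOT | TOC |
|---|---|---|---|
| ALT | 0.9 | 4.0 | 1.5 |
| Total bilirubin | 0.6 | 2.4 | 1.0 |
| ALP | 0.8 | 3.0 | 2.5 |

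- Literal rule: highest ALT 4.0 ≥3, highest bilirubin 2.4 >2, and one ALP (0.8 at Day 3) ≤2. The subject is counted.
- ALP at the draw with raised ALT: 3.0 >2. Not counted.
- Worst ALP: 3.0 >2. Not counted.

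**Step 2: all patterns.** At each of three draws, record yes or no for ALT/AST ≥3 × ULN, bilirubin >2 × ULN and ALP >2 × ULN. These are logical patterns, not expected frequencies.

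- Patterns with a transaminase elevation and a bilirubin elevation at some draw: (2³ − 1) × (2³ − 1) × 2³ = 7 × 7 × 8 = 392.
- Counted under the literal rule (any ALP ≤2 × ULN): 49 × 7 = 343. The 49 left out have ALP >2 × ULN at all three draws.
- Counted if all three criteria must be met in one draw: 8³ − 7³ = 169.
- Counted if the worst ALP must be ≤2 × ULN: 49 × 1 = 49. Of the 169 one-draw patterns, only 4³ − 3³ = 37 survive this rule, so it drops 132.
- Counted if ALP is read at a draw with ALT/AST ≥3 × ULN, with bilirubin from any draw: (4³ − 3³) × 7 = 37 × 7 = 259. This keeps all 169 one-draw patterns.

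**Step 3: the patterns at issue.** In 79 patterns ALP is >2 × ULN at every draw with a raised transaminase or bilirubin. The literal rule excludes the 49 with ALP raised throughout and counts the other 79 − 49 = 30. Reading ALP at the ALT/AST draw counts none of the 79.

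**Step 4: which draws count.** If the baseline draw counts, a subject with normal baseline ALP always meets the ALP condition. FU or unscheduled results, if used, give further chances to meet it.

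**Step 5: the paired rows.** Take AST 4 × ULN, ALT 2 × ULN and bilirubin 1.8 × ULN. The ALT row fails on ALT, the AST row fails on bilirubin (1.8 is not >2), and the Hy's Law row fails on bilirubin. With ALT and AST exchanged, the subject enters the ALT row.

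**The case against.** The row is labelled as potential cases, so a broad screen that errs toward inclusion is defensible. All laboratory data are listed with out-of-range values flagged. ALP ≥1.5 × and ≥2 × ULN have their own rows, and Table 4 flags ALP >2.0 × ULN with an increase of more than 100%. A wrongly counted subject can therefore be found and reviewed. This stands, and it limits the consequence. It does not settle which ALP value the summary count uses.

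One might say that section 20.2 already fixes the value, since results are "determined based on normal limits and the worst post-baseline value using the definitions shown below for each test". That sentence governs PCS results, and the liver list does not refer to it. Carried over to ALP, it would also drop subjects who meet all three criteria in a single draw.

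On the paired rows, ALT ≥3 × ULN with bilirubin >2 × ULN is already inside the ALT row, the Hy's Law row uses >2 × ULN for both enzymes, and single-analyte rows show the rest. That is fair: this part is a drafting inconsistency with a narrow gap.

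A reader might infer that the ALP term excludes nobody, or put a figure on how few cholestatic cases it excludes. The SAP supports neither. On post-baseline draws, a subject with ALP >2 × ULN throughout is still excluded. Any percentage depends on how long ALP stays raised. Assuming a 90% chance at the injury draw and independence, a 50% chance at each of two other draws gives 0.9 × 0.5 × 0.5 = 22.5% excluded, and 80% gives 0.9 × 0.8 × 0.8 = 57.6%. The assumption decides the answer.

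**Conclusion.** The concern holds in a limited form. As written, the ALP condition excludes only subjects with ALP >2 × ULN at every draw counted, so the row can include subjects whose ALP was raised when ALT/AST and bilirubin were raised. This rests on the literal reading of the timing clause; a programmer who applies worst ALP instead would get a smaller count and could lose true one-draw cases.

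The literal rule produces over-inclusion in one descriptive safety row. The number of subjects affected cannot be derived: the SAP gives no rate for this combination of results, and the row is restricted to subjects normal at baseline, so the full safety set is not its denominator. A reader might infer that the trial's liver conclusion would be wrong; with full listings and separate ALP rows, the documents do not support that. The primary efficacy analysis is unaffected.

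The differing bilirubin cut-offs are a confirmed, smaller inconsistency that leaves one combination of results in no combination row.

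**What to change.** In section 20.2:

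- Limit the different-draw allowance to post-baseline ALT/AST and post-baseline bilirubin.
- Evaluate ALP at the draw of a qualifying ALT/AST elevation. If several draws qualify, count the subject if any of them has ALP ≤2 × ULN.
- If ALP is missing at that draw, keep the subject as a potential case and mark ALP as missing. Borrowing an earlier value could bring back the same Day 3 ALP.
- Report both bilirubin cut-offs (>1.5 × and >2 × ULN) for both ALT ≥3 × ULN and AST ≥3 × ULN.

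The cost is a few sentences and two more table rows, using data already collected. The screen becomes slightly narrower, but all laboratory data remain listed. One looseness stays by design: a subject with ALP ≤2 × ULN at the ALT/AST draw whose bilirubin rises later together with ALP is still counted, which suits a screen for potential cases.
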